## Abstract

**Introduction::**

Stroke survivors are commonly at risk of functional decline following discharge from rehabilitation, which increase their susceptibility to falls, dependency in activities of daily living and emotional disturbances. To combat these, continued therapy is important. Home-based therapy (HBT) has been shown to be useful in maintaining functional performance and quality of life of chronic stroke survivors. However, evidence on its effectiveness remains limited, while no studies are available to date which report the benefit of HBT on stroke survivors self-efficacy and emotional status. Therefore, this study aims to assess the effectiveness of post-discharge HBT in comparison to usual practice on functional outcome (mobility and gait speed), self-efficacy and anxiety level among stroke survivors.

**Methods::**

This is an assessor-blinded randomized control trial comparing 2 types of intervention which are HBT (experimental group) and usual practice (UP) (control group). Based on sample size calculation using GPower, a total number of 42 participants will be recruited and allocated into either the HBT or the UP group. Participants in HBT group will receive a set of structured exercise therapy consisting of progressive strengthening, balance and task-related exercises. While participants in UP group will receive a usual “intervention” practised by rehabilitation professional prior to discharging stroke patients from their care. Both groups are advised to perform the given interventions for 3 times per week for 12 weeks under the supervision of their caregiver. Outcomes of interventions will be measured using timed up and go test (for mobility), ten-meter walk test (for gait speed), stroke self-efficacy questionnaire (for self-efficacy) and hospital anxiety and depression scale (for anxiety level). All data will be analyzed using descriptive and inferential statistics.

**Discussion::**

This study will provide the information on the effectiveness of HBT in comparison to UP among stroke population who are discharged from rehabilitation. Findings from the study will enable rehabilitation professionals to design effective discharge care plan for stroke survivors in combating functional decline when no longer receiving hospital-based therapy.

**Trial registration::**

Australian New Zealand Clinical Trials Registry, ACTRN12619001182189 (last updated 22/11/2019).

## Introduction

1

Stroke is a notable global health problem and cause of disability worldwide.^[1]^ Generally, mortality rate of acute stroke has reduced with the advancement of medical care; most countries now have an increasing number of stroke survivors hence those living with disability.^[2]^ This increased prevalence of stroke-related disability which requires continuous and long-term rehabilitation and healthcare support places great burden on healthcare system.^[2]^

Rehabilitation remains the mainstay of treatment to combat post-stroke disability.^[3]^ The service is provided during hospitalization for acute and sub-acute stroke, and normally continued in out-patient settings once the stroke patient is discharged home. Physiotherapy is part of the multidisciplinary rehabilitation program that aim to improve strength, balance, coordination, endurance and flexibility of stroke patients.^[3]^ Therapy sessions for stroke are normally provided 2 to 3 times per week and continued for as long as 1 year or more post-onset depending on the patients needs.^[3]^ Shortage of manpower to cater for the fast-growing number of new stroke patients which outnumbered the discharged patients has however hinder the provision of further therapy and monitoring once the patient is discharged from hospital-based rehabilitation.^[4–6]^ In usual practice, stroke patient will be provided with home exercise program in a form of written or verbal prescription and advised to try maintain functional performance upon discharged from rehabilitation.^[4]^

Studies have shown that functional decline occurred in stroke survivors post-discharge from rehabilitation due to poor exercise adherence, lack of motivation, musculoskeletal issues and fatigue.^[7]^ Past studies that assessed the function of stroke survivors at 1 year or more post-discharge reported deterioration of gait speed and balance ability among the survivors at several months of discharge.^[8,9]^ Therefore, the continuity of rehabilitation at post-discharge episode is crucial to prevent functional deterioration in stroke survivors. There is a need to review the existing “usual practice” and develop a better approach. A few studies have shown that functional deterioration can be impeded with a rehabilitation or care intervention based at home.^[9]^ Home-based therapy (HBT) was able to cease the deterioration and improve the performance of activities of daily living (ADL) in stroke patients.^[10,11]^ Thus, HBT might be an alternative approach for stroke survivors who require long-term management. However, the overall effects of HBT on post-discharged stroke patients remain unknown due to scarcity of research on this population. Self-efficacy and emotional aspect of stroke survivors play an important role in determining quality of life in long term post-stroke,^[12]^ but no studies have evaluated the effectiveness of HBT with regards to these outcomes. Therefore, the purpose of this study is to determine the effectiveness of HBT in stroke survivors following discharge from rehabilitation in term of functional outcome (mobility and gait speed), self-efficacy and anxiety level. This study also aims to assess the feasibility of HBT plan on this population.

## Methods

2

### Study design and setting

2.1

This is an assessor-blinded randomized control trial comparing 2 types of intervention which are home-based therapy (experimental group) and usual practice (control group). The study will be conducted at 2 public rehabilitation hospitals, namely Universiti Kebangsaan Malaysia Medical Center and Cheras Rehabilitation Hospital. Both hospitals are main referral centers for stroke cases in Kuala Lumpur, the capital of Malaysia. List of all stroke patients to be discharged from the 2 hospitals following rehabilitation will be used to recruit participants adequately. Figure 1 shows the flow of the study.

**Figure 1 F1:**
[figure not shown]
Flow of the Study.

### Study participants

2.2

Potential participants will be recruited by the main researcher; inclusion criteria are as follows:

1.Clinically diagnosed as stroke by a medical officer.2.Completed hospital-based rehabilitation and scheduled for discharge.3.Age 18 to 80 years old. (to minimise risk of frailty which is prevalent in those above 80)^[13]^4.Availability of carer to monitor home-based interventions.5.Score 3 or more on functional ambulation categories (FAC) (3: ambulator-dependent for supervision; 4: ambulator-independent level surface only; 5: ambulator-independent)

Exclusion criteria are:

1.Score below 20 on Montreal Cognitive Assessment (MoCA) which indicates presence of cognitive impairment.2.Score 4 or more on a Modified Rankin Scale (4: moderate severe disability; 5: severe disability; 6: death).3.Attended by a home physiotherapist after discharged from HOS.4.Score above 11 on Hospital anxiety and depression scale -depression subscale (HADS-D) which indicates moderate to severe depression.5.Presence of other medical conditions such as severe neurological and musculoskeletal disorders or comorbidities.

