### Participants allocation

2.3

Stroke survivors will be randomized into either HBT (experimental group) or UP (control group) using stratified randomization method, with the use of microsoft-excel 2016 software by an independent researcher. Stratification variables are age, consisting of adult (18–59 years), young-old (60–74 years) and old-old (75–85 years), and disability level, namely 1 (no significant disability), 2 (slight disability) and 3 (moderate disability). Using the software, a random number column of subjects will be generated, and by using the sort function, recruited subjects will be stratified according to the sequence of age, disability level and random number. Subjects are then alternately allocated into each trial arm according to their age and disability level categories. Therefore, both the HBT and UP trial arm will consist of subjects with the different age and disability levels.

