## Discussions

3

The decline in stroke survivors functional performance following discharge from formal rehabilitation place the survivors at increased risk of stroke recurrence, falls and emotional disturbances which eventually lead to reduced quality of life.^[22,23]^ As such, there is a need to ensure the continuity of therapy to prevent these negative consequences among the stroke survivors. Due to the high workload and manpower shortage in many rehabilitation centers particularly in developing countries, extended stroke rehabilitation in hospital settings is difficult. Many stroke survivors are discharged rather prematurely when further functional improvement is still possible with regular rehabilitation therapies. There is also no monitoring of functional performance once the stroke survivors are discharged from rehabilitation service, raising concern on the needs for proper discharge care plan.

Training stroke survivors and caregivers to perform structured home therapy which focuses on therapeutic exercises may be a beneficial strategy to fill these needs. Studies have shown that home-based therapy can be as effective as hospital-based program in preventing functional deterioration of stroke survivors^[11,24,25]^ However, evidence on its effectiveness, particularly among post-discharged stroke patients are still limited to inform clinical practice, which warrants more studies on this topic area. Further, past studies have not included psycho-behavioral and emotional aspects, 2 important determinants of quality of life among stroke survivors^[26]^ in their assessment of intervention outcome. Therefore, this study is proposed to fill these gaps in knowledge and strengthen evidence on the benefit of home-based therapy for stroke survivors. This study will also compare home-based therapy with the existing common practice for discharged stroke survivors and provide information whether HBT is a better approach for this group of population in preventing long-term functional problems. It is our hope that findings from this study can be used to enable rehabilitation professionals to design an effective care plan for stroke patients who are scheduled for discharge and as a reference for future studies regarding home-based therapy and post-discharge care.

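### Time since stroke is open at entry and absent from both the strata and the stated model, which may cost precision at 21 per arm

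*Protocol article*

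**What the plan says.** **Entry.** Under Study participants (2.2), the two criteria that bear on timing are "Clinically diagnosed as stroke by a medical officer" and "Completed hospital-based rehabilitation and scheduled for discharge". Neither the inclusion nor the exclusion list limits the interval since the stroke.

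**Spread.** The Introduction says that therapy sessions may be "continued for as long as 1 year or more post-onset depending on the patients needs".

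**Course after discharge.** The Discussions section says "Many stroke survivors are discharged rather prematurely when further functional improvement is still possible with regular rehabilitation therapies". The Introduction says that "functional decline occurred in stroke survivors post-discharge from rehabilitation", and that earlier studies "reported deterioration of gait speed and balance ability among the survivors at several months of discharge".

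**Allocation.** Under Participants allocation (2.3), "recruited subjects will be stratified according to the sequence of age, disability level and random number". No other factor is used.

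**Analysis.** Data analysis (2.8) states a mixed ANOVA that reports time, group and their interaction for each outcome. Assessment of outcomes (2.6) gives two visits, baseline and week 12. Sample size (2.7) gives 42 participants, 21 per arm, for the within-between interaction at 80% power and alpha 0.05.

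**The concern.** Discharge puts everyone at the same point in the care pathway, but not at the same time after the stroke. By the protocol's own account that time can reach a year or more. If expected change over 12 weeks depends on time since onset, participants with different expected change are pooled.

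With two visits, the time-by-group interaction is a comparison of change scores between arms. Change scores remove differences in starting level but not differences in slope. Any variation in slope linked to time since onset therefore goes into the error term. An arm that by chance holds more recently affected participants also keeps that imbalance in its estimate. With 21 per arm, both effects could be large enough to matter. Mobility and gait speed, the outcomes for which the article describes change after discharge, are among those analysed this way.

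**Working it through.** **Inputs from the protocol article.** 42 participants, 21 per arm; two visits; power 80%; alpha 0.05; interaction test (2.6, 2.7). No effect size, correlation, SD or distribution of time since onset is given.

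**The plan's own figure.** For two groups and two visits, the G*Power interaction test has noncentrality λ = f²·N·2/(1 − ρ) with 1 and N − 2 degrees of freedom. The figure of 42 cannot be reproduced, because f and ρ are not stated. It would follow, for example, from f = 0.222 at ρ = 0.5, f = 0.262 at ρ = 0.3 or f = 0.172 at ρ = 0.7. All of these amount to the same two-sample comparison of change scores: λ = d²·21/2, with d = 0.886 SD of change for 80% power on 40 df.

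**Assumption.** Let R² be the share of change-score variance explained by time since onset. The documents give no value, so a range is shown.

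**Power without adjustment.** Take an effect that has 80% power once this variance is removed (d = 0.886 in units of the residual SD). Left unadjusted, the SD grows by 1/√(1 − R²), so the effective difference is 0.886·√(1 − R²). For R² = 0.20 this is 0.886 × 0.894 = 0.793. The total N that restores 80% is about 42/(1 − R²). The last column takes the other reading, in which the planning SD already contains this variance. The unadjusted analysis then has its planned 80%, and adjustment raises d to 0.886/√(1 − R²) on 39 df.

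| R² | Effective d, unadjusted | Power, unadjusted | Total N for 80% | Power after adjustment if the planning SD already includes this variance |
|---|---|---|---|---|
| 0.05 | 0.864 | 78% | 44 | 82% |
| 0.10 | 0.841 | 76% | 47 | 84% |
| 0.20 | 0.793 | 71% | 53 | 88% |
| 0.30 | 0.741 | 65% | 60 | 92% |

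**Chance imbalance at 21 per arm, ignoring the strata.** For a continuous factor, the standardised difference between arms has standard error √(2/21) = 0.309. It exceeds 0.3 SD in 33% of allocations and 0.5 SD in 10.5%. If time since onset is instead split into early and late, and between 12 and 21 of the 42 are early (assumed), the hypergeometric probability that the arms differ by 4 or more early participants is 18% to 35%. The value moves up and down with the count, because the difference is always even for an even total and odd for an odd one.

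**Bias and type I error.** In 40,000 simulated trials per setting with the factor ignored, rejection under no effect was 5.0–5.1% at R² = 0, 0.2 and 0.4, and average bias was about 0. Power at d = 0.886 was 80%, 71% and 58%.

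**Cost of adjusting for a useless covariate.** With one residual degree of freedom fewer (39 instead of 40), power is 79.95% against 80%.

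**The case against.** **Different courses.** A reader might infer that the trial mixes people still recovering with people already declining. The documents do not support this. Everyone enters at scheduled discharge, and the Introduction places decline after it. The Discussions section makes further improvement conditional on regular therapy, and no section ties the direction of change to time since onset. What stands is narrower: time since onset may vary widely, and expected change may vary with it.

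**Bias.** A reader might also infer that an imbalance would pass for a treatment effect. Over repeated randomisation it is ordinary sampling error, already covered by the 5% level, and the simulation confirms this. Only precision, and the estimate in a particular unbalanced sample, are affected.

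**Size.** R² is assumed throughout. If the planning SD came from an equally mixed population, power is not below plan, and the point becomes a gain forgone. The chance of a given standardised imbalance depends on the number per arm and not on how wide entry is; wide entry only makes an imbalance matter more.

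**Already handled, or left to another document.** Entry at discharge looks deliberate and suits the question. Disability level may absorb part of the variation, but it describes current status, and two people at the same level can have different slopes. An analysis plan that is not shown could name covariates, and the stroke date may already be collected. That limits the point to what the article does fix: the open entry criterion, the two strata and the model's effects. It does not remove it, because the stated model can be improved at almost no cost.

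**Conclusion.** The concern holds as a question of efficiency, not of validity. Entry has no limit on time since stroke, allocation balances only age and disability level, and the stated model has no term for time since onset. The comparison remains unbiased and the type I error stays at 5%.

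The loss depends on a prognostic strength that the documents do not give. It is at most about 2 points of power if R² is 5% or less, and about 4, 9 and 15 points at 10%, 20% and 30%. These losses assume that the planning SD leaves this variance out. The change should be made, with medium confidence in how much it gains.

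**What to change.** At baseline, take the date of the qualifying stroke from the hospital record. Before outcome data are seen, pre-specify log(time since onset) as a covariate in the between-arm comparison of each outcome. If the two-visit mixed ANOVA is kept, enter it as a covariate-by-time term; a main effect alone would not adjust the interaction. Show its distribution by arm in the baseline table.

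Eligibility, strata, visits and interventions stay unchanged. The cost is one baseline field and one of 40 residual degrees of freedom. If time since onset is not prognostic, nothing is gained.

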### Participants allocation

2.3

Stroke survivors will be randomized into either HBT (experimental group) or UP (control group) using stratified randomization method, with the use of microsoft-excel 2016 software by an independent researcher. Stratification variables are age, consisting of adult (18–59 years), young-old (60–74 years) and old-old (75–85 years), and disability level, namely 1 (no significant disability), 2 (slight disability) and 3 (moderate disability). Using the software, a random number column of subjects will be generated, and by using the sort function, recruited subjects will be stratified according to the sequence of age, disability level and random number. Subjects are then alternately allocated into each trial arm according to their age and disability level categories. Therefore, both the HBT and UP trial arm will consist of subjects with the different age and disability levels.

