- participant with fair standing balance
• Step and reach to targets
- participant with good standing balance
• Sit and reach to targets
- participant with poor standing balance
5. Walk and pivot turn exercise
6. Sideway walking exercise – either one exercise from below according to participants standing balance
• Cross over side step
- participant with good standing balance
• Walk sideway
- participant with fair/good standing balance
7. Walk with stepping exercise – either one exercise from below according to participants standing balance and lower limb muscle strength
• Walking Lunge
- participant with fair/good standing balance and muscle strength above 3/5
• Walking with big step
- participant with fair standing balance and muscle strength above 3/5
8. Wall push-ups
9. Arm Exercise – any one exercise from the list below according to participants upper limb muscle tone and strength
• Upper limb proprioception exercise
- participant with muscle tone above 1+
• Upper limb active range of exercise
- participant with muscle tone above 1 and muscle strength below 3/5
• Upper limb strengthening exercise
- participant with normal muscle tone and muscle strength 3 and above

HBT = home-based therapy.

Meanwhile participants in UP group will be advised to perform exercises as prescribed by the therapist prior to discharged from physiotherapy service. This is the common practice among the attending therapists when discharging stroke patients. Similarly, participants will be monitored in term of exercise adherence and occurrence of any potential adverse effects related to exercise such as muscle soreness and cramps via telephone call once in every 2 weeks. Participants will also be asked to record their exercise practice in a logbook.

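### Allocation in a two-hospital trial of 42 leaves hospital out, so the hospital mix of the arms is left to chance: unbiased on average, but an avoidable loss of precision.

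*Protocol article*

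**What the plan says.** Section 2.1 states: "The study will be conducted at 2 public rehabilitation hospitals". Patients come from the discharge lists of both, so each participant's hospital is known at recruitment.

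Section 2.3 describes the allocation in full. There are two stratification variables: age in three bands and disability in three levels. A random number is generated, and "recruited subjects will be stratified according to the sequence of age, disability level and random number". Then: "Subjects are then alternately allocated into each trial arm according to their age and disability level categories". Hospital is not among the sort keys.

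Section 2.4 defines the control treatment by reference to routine care: "participants in UP group will be advised to perform exercises as prescribed by the therapist prior to discharged from physiotherapy service". It adds: "This is the common practice among the attending therapists when discharging stroke patients". The HBT arm, by contrast, follows the fixed nine-exercise programme of Table 1.

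Section 2.8 analyses each outcome by mixed ANOVA with time, group and time-by-group effects and names no hospital factor. Section 2.7 sets the sample at 42, 21 per arm.

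**The concern.** Hospital plausibly predicts change over the 12 weeks. Each hospital delivers the preceding rehabilitation and makes the discharge decision that creates eligibility, and the therapists who write the usual-practice prescription work there. In a trial of 42, a prognostic factor that is neither balanced at allocation nor modelled can differ visibly between the arms, and part of any HBT–UP difference may then reflect where patients were treated. Allocation cannot be redone at the analysis stage, and including a factor already on file costs very little.

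**Working it through.** **Inputs.** From the article: two hospitals (2.1), nine age-by-disability strata and a sort-then-alternate scheme (2.3), 42 participants with 21 per arm (2.7). The article gives no hospital split, no hospital difference in outcome and no effect size behind the 42, so these are assumed below.

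**1. Scale.** The 42 cannot be reproduced because the effect size and the correlation are not stated. Solving backwards, 21 per arm gives 80% power at two-sided 0.05 for a difference in change of about 0.89 SD. This holds whatever the correlation (f = 0.31 at correlation 0, 0.22 at 0.5, 0.14 at 0.8).

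**2. Chance imbalance.** Assume 21 patients per hospital. Let X be the number from hospital A in the HBT arm. Ignoring the strata, X is hypergeometric: P(X = k) = C(21,k)² / C(42,21), with C(42,21) = 538,257,874,440.
- 14:7 or worse: 2 × [C(21,14)² + … + C(21,21)²] / C(42,21) ≈ 2 × 1.692×10¹⁰ / 5.383×10¹¹ = 0.063. The gap in hospital share is 14/21 − 7/21 = 7/21 = 33 points.
- Exactly 13:8 either way: 2 × 203,490² / 5.383×10¹¹ = 0.154. So 13:8 or worse is 0.154 + 0.063 = 0.217, a gap of at least 5/21 = 24 points.
- Var(X) = 21 × 0.5 × 0.5 × 21/41 = 2.69, so SD(X) = 1.64. The SD of the gap in share is 2 × 1.64 / 21 = 0.156.

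Other splits give less imbalance: a gap of 20 points or more has probability 10% at 28:14 and 7% at 32:10.

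**3. Shift in the estimate.** Shift = gap in share × hospital difference in change. With an assumed difference of 0.5 SD:
- 13:8: 0.238 × 0.5 = 0.12 SD, about 13% of 0.89 SD.
- 14:7: 0.333 × 0.5 = 0.17 SD, about 19% of 0.89 SD.
- Typical (one SD of the gap): 0.156 × 0.5 = 0.08 SD.

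The standard error of the comparison is √(2/21) = 0.31 SD, so these shifts are about 0.4, 0.5 and 0.25 of one standard error.

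**4. Simulation of the stated scheme.** There were 5,000 trials per scenario, with hospital drawn 50:50, an assumed age and disability mix independent of hospital, and one continuous alternation.
- Hospital ignored: under no effect the mean estimate was 0.003 to 0.012 SD and type I error 4.5% to 5.2%. The SD of the gap was about 0.155, and a gap of 20 points or more occurred in 16% to 17% of trials. This is below 22% because the hospital total varies: when it is even, the smallest gap above 20 points is 6 participants rather than 5.
- Hospital as first sort key: the SD of the gap fell to 0.034, and gaps of 20 points or more did not occur.

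Power for a true effect of 0.88 SD:

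| Hospital difference | Hospital ignored | Hospital in model only | Hospital in allocation and model |
|---|---|---|---|
| 0.5 SD | 78% | 79% | 80% |
| 1 SD | 70% | 79% | 80% |

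Stratifying without the model term is not enough. At a 1 SD hospital difference, type I error fell to 3.0% and power was 72%, because hospital variation stayed in the error term.

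**5. Restarting alternation.** Section 2.3 can also be read as alternation that restarts in each cell. Across both readings, a further simulation put the SD of the gap with hospital as first key between 0.00 and 0.07, against about 0.16 without it, with almost no loss of age balance.

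**The case against.** The strongest reply is that nothing here invalidates the comparison. Within age and disability, patients of both hospitals are ordered by a random number and then alternated, so both hospitals feed both arms, and the standard error already covers chance imbalance. A reader might infer that hospital is confounded with treatment. The documents do not support that: the estimate is unbiased on average and type I error stays near 5%. The 0.12 and 0.17 SD shifts are tail cases on an assumed hospital difference. At 0.5 SD the typical shift adds about 0.08² / 0.31² ≈ 7% to the sampling variance, and power changes by about two points. All of this stands.

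It can also be said that a hospital term in the model belongs to an analysis plan that is not shown. That is fair, and the missing term alone would not be a point. The allocation scheme, however, is set out completely in the article, and a later analysis plan cannot change it.

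A second tempting inference is that a therapist who learns the arm could tailor the prescription, or that the comparator is undefined. The article does not say this happens. It places the prescription before discharge from physiotherapy, recruits patients already scheduled for discharge (2.2), and nowhere says that the therapist learns the allocation. The exact order is operational detail that a condensed article may leave out. The remark that patients are "provided with home exercise program in a form of written or verbal prescription" is background in the Introduction, not the trial's definition of UP. UP participants keep logbooks and are telephoned every two weeks. Variation between therapists is inherent in a usual-practice control and bears on generalisability rather than validity.

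**Conclusion.** The point holds as a matter of chance imbalance and precision. Hospital is known, plausibly prognostic and absent from a fully specified allocation. The imbalance probabilities (22% and 6%) rest on an assumed 21:21 hospital split and fall with less even splits. The shifts rest on an assumed hospital difference of 0.5 SD. The cost of leaving hospital out altogether ranges from about 2 points of power at 0.5 SD to about 10 at 1 SD, and is nil if the hospitals do not differ. Most of that power comes back through the model term; what the extra sort key adds is that the arms are visibly comparable by hospital in the one trial that will be run. The case for change rests on the low cost of the remedy, not on a flaw that would overturn the result.

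**What to change.** In Section 2.3, make hospital the first sort key, ahead of age, disability and random number. In Section 2.8, add hospital as a between-subject factor in the outcome model.

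The cost is more and thinner cells: 3 × 3 × 2 = 18 instead of 9, or 42/18 ≈ 2.3 participants per cell. Merging the two oldest age bands gives 2 × 3 × 2 = 12 cells, or 3.5 per cell. The model gives up one degree of freedom. Section 2.3 should also say whether alternation runs on down the sorted list or restarts in each cell. If it runs on, the arms differ by at most one participant within each hospital. If it restarts, every odd-sized cell can add one, so balance is close but not within one.

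Optionally, file a copy of each participant's usual discharge prescription before allocation is released, so that UP can be described by hospital. The downside is that any verbal prescription must be written down, which slightly formalises usual practice.

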### Sample size

2.7

GPower software version 3.0.10 was used to estimate required sample size for this study. This study used mixed model analysis of variance (ANOVA) to analyze time, group and interaction effects of the interventions. Therefore F-test (ANOVA repeated measure, within-between interactions) were chosen. The study power was set at 80% and alpha value set at 0.05. Based on these, a minimum sample of 42 subjects is required, i.e., 21 participants in each arm.

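### Sorting recruited subjects and then alternating arms is sound only for a complete list or large batches; run patient by patient it either changes earlier arms or becomes predictable, and Rankin 0 has no stratum

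*Protocol article*

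**What the plan says.** Section 2.3 (Participants allocation) gives the procedure to an independent researcher working in Excel. A column of random numbers is generated, and "recruited subjects will be stratified according to the sequence of age, disability level and random number". The arm then follows from list position: "Subjects are then alternately allocated into each trial arm according to their age and disability level categories". The stratifiers are three age bands, the highest being "old-old (75–85 years"), and three disability levels numbered 1 to 3.

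Elsewhere in the article:
- Section 2.1: candidates come from the lists of stroke patients about to be discharged from the two hospitals.
- Section 2.2: entry requires completed hospital rehabilitation and a scheduled discharge. The age criterion is "Age 18 to 80 years old", and only Modified Rankin scores of 4 or more are excluded.
- Section 2.2 also says "Potential participants will be recruited by the main researcher". The same person obtains consent (section 2.9) and trains participants and caregivers before the home sessions (section 2.4).
- Section 2.7: "a minimum sample of 42 subjects is required, i.e., 21 participants in each arm".

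**The concern.** In this scheme the random number only orders people who are already on the list; the arm is then fixed by alternation. The scheme therefore depends on how many people are listed when the sort is run, and section 2.3 does not say. Patients reaching discharge would ordinarily arrive one at a time, and a sort-then-alternate rule cannot be applied to single arrivals without turning into something else.

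What is at stake is concealment of the next assignment. A recruiter who can foresee the next arm can, knowingly or not, influence who is enrolled and when. The last exclusion criterion, on other medical conditions and comorbidities, leaves room for judgement. Selection at entry cannot be reliably corrected in the analysis, and the blinded assessor in section 2.6 does not prevent it. With 21 per arm, a few steered enrolments would matter.

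A second, separate question is whether every eligible patient has a stratum.

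**Working it through.** **Inputs.** N = 42, 21 per arm (section 2.7). Strata: 3 age bands × 3 disability levels = 9 (section 2.3). Entry at scheduled discharge (sections 2.1 and 2.2).

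**The plan's own figure.** The article gives 42 without the effect size f or the correlation ρ between the two measurements, so it can only be matched, not reproduced. With λ = f²·N·m/(1−ρ) and m = 2 time points, f = 0.225 and ρ = 0.5 give λ = 0.225² × 42 × 2 / 0.5 = 8.5, power 81%, and a required N of 42. Nothing below depends on that match; 42 is taken as stated.

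**Ways the stated procedure can be run.**

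1. *One sort after all 42 are recruited.* Within each stratum the order is random, so alternation down the list gives an unpredictable 21:21 split. Statistically this is sound. In practice the first recruits would wait for the last before starting a programme meant to follow discharge, and no section provides for that wait.

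2. *Sort in batches.* Large batches behave like case 1. As batches shrink they approach case 4. No batches are described.

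3. *Re-sort the growing list at each arrival.* A newcomer whose random number is lower than that of someone already in the stratum is inserted above that person, and alternation then gives the earlier subject the other arm. In simulation (2,000 runs, 42 subjects, 9 equally likely strata), the share of subjects whose arm changes at least once is:
   - about 54% with alternation within strata;
   - about 90% with alternation down the whole list.

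   This cannot be used once treatment has begun.

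4. *Alternate within stratum in order of arrival.* The random number then has no role. Only the first patient in each stratum is unknown:
   - assignments certain to someone who knows the previous one in that stratum: at least 42 − 9 = 33, and 33/42 = 79%;
   - expected correct-guess rate, counting each first patient as a coin toss: (33 + 9 × 0.5)/42 = 37.5/42 = 89%, against 50% under simple randomisation.

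   Simulation with an assumed uneven stratum mix gives about 90%, so the result does not hinge on equal strata.

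**Who could use this.** In case 4 the recruiter needs the new patient's age and disability, which screening supplies, and the last arm in that stratum, which delivering the training would probably reveal.

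**Strata against eligibility.**

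| | Eligible (2.2) | Strata (2.3) | Consequence |
|---|---|---|---|
| Age | 18–80 | 18–59, 60–74, 75–85 | Top band too wide; nobody left out |
| Disability (read as Rankin) | 0–3 | 1, 2, 3 | A score of 0 cannot be placed |

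**The case against.** The best defence is that the text, read literally, is not predictable. It sorts recruited subjects by random number and leaves this to an independent person; it nowhere says that alternation follows order of arrival. Rolling entry is an inference, the flow figure is not available, and a condensed article may leave batching and concealment to the full protocol. All of that stands as a limit on the claim. It does not remove the point, because the article states a mechanism, and that mechanism works only under a timing that the article does not give and that sits awkwardly with entry at discharge. The independent researcher reduces the risk, but under arrival-order alternation would not remove it.

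A reader might go further and infer any of the following, none of which the document supports:

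- *The allocation is fully predictable, or selection bias is established.* Predictability belongs to case 4 or very small batches, which the text does not state.
- *The arms will be noticeably unequal.* If every stratum restarted with the same arm, the imbalance would equal the number of odd-sized strata, about 4.5 patients on average with equally likely strata. Section 2.3 does not say that strata restart this way, and one alternation down the whole sorted list gives exactly 21:21.
- *Nine strata are too many for 42 patients (4.7 each).* Sorting and alternating tolerates small cells. Sparse cells are a greater problem for permuted blocks, which is why the fix uses few strata.
- *Hospital must be a stratifier because* "The study will be conducted at 2 public rehabilitation hospitals". The article does not show that control exercises differ by hospital. Stratifying by site is an option, not a correction.

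**Conclusion.** The concern holds in a conditional form. As written, section 2.3 is a proper allocation only for a complete list or large batches. Applied patient by patient, it either reassigns earlier subjects (roughly 54% to 90% changed at least once, with equally likely strata) or becomes alternation in which at least 33 of 42 assignments (79%) follow from the one before in the same stratum. This rests on two inferences: that entry is rolling, and that the main researcher learns earlier arms through the training. Bias has not been shown; what is shown is that the stated mechanism does not protect against it under the most natural pattern of entry.

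The missing stratum for Rankin 0 is a real gap, provided that disability level means the Rankin grade. The labels in section 2.3 and the exclusion criterion in section 2.2 point that way, although section 2.3 does not name the scale. How many patients would score 0 is unknown. The 75–85 band is an inconsistency without practical effect.

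**What to change.** Rewrite section 2.3 so that:

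1. the independent researcher generates the sequence before first enrolment, using permuted blocks of randomly varied size within a small number of strata, or minimisation with a random element;
2. the sequence is concealed from the main researcher, and each assignment is released only after consent and baseline assessment, for example by telephone or sequential sealed envelope;
3. the disability scale is named and its levels include Rankin 0, and the top age band ends at 80, so that the strata cover exactly the eligible range.

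If a single complete list or large batches were intended, section 2.3 should say so, give the batch size, and show that the wait is workable for patients being discharged.

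The cost is a rewritten section and a new list. No extra staff are needed, because the independent researcher is already in the plan. The downside is fewer stratification cells, and so less exact balance on the combination of age and disability.
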